### Inclusion and exclusion criteria

VA sites are eligible if they are below the VA national median on GI cancer screening completion, where HCC screening is defined as abdominal imaging within the prior six months for Veterans with cirrhosis, and CRC screening is defined as receipt of colonoscopy within six months for Veterans with a positive stool test. We will include 24 sites in the HCC trial and 32 sites in the CRC trial. Veterans will be included and passively cluster randomized to their sites of primary care if they are 1) at least 18 years old, 2) eligible for CRC or HCC screening, and 3) enrolled in VA care in a recruited site with at least one encounter in the prior 18 months. For the HCC trial, we will define Veteran eligibility as having at least two ICD codes for cirrhosis or its complications in the electronic medical record. For the CRC trial, we will include Veterans over 45 years old who have had an abnormal fecal immunochemical test (FIT) or other screening stool test in the last 18 months. We will exclude Veterans who are not eligible for cancer screening due to receiving end of life care, defined as having a code for hospice, or who have a prior diagnosis of the cancer of interest. We will include healthcare providers or related staff working at participating VA sites who are engaged in CRC or HCC screening pathways.

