### Outcomes

The study outcomes are illustrated in Table 2 and were mapped to the RE-AIM framework [68, 69]. Each trial is powered to assess differences in reach of GI cancer screening between the two arms at 12 months from baseline. The primary outcome for HCC screening is the receipt of HCC screening by ultrasound or contrasted imaging study. We will assess patients with a diagnosis of cirrhosis at each site, and evaluate whether they had HCC screening within the prior six months. The primary outcome for CRC screening is receipt of colonoscopy after an abnormal stool test for occult blood. For the CRC trial, we will assess whether patients with an abnormal stool-based CRC screening test completed a colonoscopy within six months. We will assess Effectiveness and Maintenance as patient-level outcomes, and Adoption and Implementation (including feasibility, acceptability, appropriateness) as site-level outcomes. Fidelity to and adaptations of the implementation strategies will be tracked monthly using standard data collection forms.

**Table 2 Tab2:** Outcome measures

Outcome	Specific Measure	Timepoints
**Reach** of CRC screening	CRC screening completion among patients with positive stool tests, representativeness of the population that receives screening (EMR)	Baseline & 12 months
**Reach** of HCC screening	HCC screening among Veterans with cirrhosis representativeness of the population that receives screening (EMR)	Baseline & 12 months
**Effectiveness** of screening	Tumor/polyp/lesion detection; linkage to cancer care (EMR) health benefits for rural and Black populations (EMR); change in quality of life (PRO)	Baseline & 12 months
**Adoption**	> 65% or 80% of eligible Veterans receive HCC or CRC screening, respectively (EMR)*,* reasons for non-adoption (Qu)	Baseline & 12 months
**Implementation**	How screenings and strategies are delivered	Ongoing
Feasibility	Feasibility of Intervention Measure [60] (Pr); meeting attendance, Qu	12 months
Acceptability	Acceptability of Intervention Measure [60] (Pr); Qu	12 months
Appropriateness	Intervention Appropriateness Measure (Pr); Qu	12 months
Fidelity	Whether strategies & screenings are delivered as intended (St)	Monthly
Adaptation	Changes to strategies over time (St, MADI, Qu)	12 months
Potential harm	Inequitable access (EMR), decreased engagement, trust, activation (EMR, Pt, Qu), provider mistrust, poor communication, burnout (Pr, Qu) [61, 62]	12 months

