### Analysis

Results will be presented overall for each trial. We will use generalized linear mixed models (GLMMs) to assess the primary outcome of reach at 12 months. Time, intervention status, and the interaction will be modeled as fixed effects. Random effects will be included for clustering by site and Veteran. The parameters in the regression model and variance components will be estimated using the Maximum Likelihood or Restricted Maximum Likelihood. We will conduct a secondary analysis of the CRC outcome evaluating time to colonoscopy after abnormal stool test, using appropriate time-to-event models and conduct a sensitivity analysis that includes only Veterans with at least six months of follow-up after stool testing.

To understand whether and how the effectiveness of IF vs. PN varies between patients’ subgroups, we will conduct pre-specified exploratory secondary heterogeneity of treatment effect analyses. We will fit the same GLMMs as described above and include higher order interaction terms with subgroups of patients (e.g., rural vs. urban dwelling Veterans). The null hypothesis of homogenous treatment effect between Veterans within different subgroups for each outcome will be examined via interaction analysis (three-way interaction of time, treatment, and the subgroup of patients with decreased baseline rates [e.g., rural Veterans]; two-way interaction of treatment and subgroup of patients in the absence of a significant three-way interaction effect) using the same ANOVA type III Wald test based on either F- or Chi-square statistics as appropriate. In the presence of statistically significant treatment heterogeneity, we will fit a separate GLMM model for each subgroup of participants. For each outcome, the change scores from baseline to 12 months and their difference among the two treatments will be estimated using least square estimate with 95% confidence intervals for subgroups of patients.

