### Sample size and power

Power calculations were informed by pilot data, literature, and similar studies. Estimates included VA data to calculate the mean number of eligible patients per site (811 ± 387 for HCC, and 429 ± 265 for CRC), coefficient of variance of cluster sizes (0.48 for HCC and 0.631 for CRC) within-person correlation of 0.2 (for HCC), and baseline screening rates. We applied a moderate ICC of 0.03 but varied the ICC up to 0.1 in our models. Based on literature demonstrating ~ 17% improvement in cancer screening with PN and ~ 9% improvement in screening with IF, we powered the study to detect an expected difference in screening rates between the PN vs. IF arms of 0.085 [24–47].

The cps.did.binary function in the R package clusterPower [72] was modified to include coefficients of variation of the cluster sizes using simulations (average of 1000 simulated data = 0.48 for HCC; 0.631 for CRC) and account for within-person and within-site correlation and validated these calculations using simulations that allow the hierarchical clustering [73]. Varying the parameters widely (e.g., difference in effect size as low as 0.03 between arms) and conducting over 1000 simulations, the HCC models demonstrated > 85% power with 12 sites per arm, and the CRC models retained > 80% power with 16 sites per arm.

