## Discussion

This research protocol addresses a critical gap in implementation science. Though implementation literature recommends that strategies be selected to address specific implementation barriers (i.e., strategies are not “one size fits all”),[21, 22, 74–77] it remains unclear how to operationalize this recommendation. This study will test whether and when PN (a one-size-fits-all, patient-facing approach) works better than working with sites to select strategies based on barriers. Comparing how these strategies work across two types of cancer screening will offer further insights into when to apply one-size-fits-all PN vs. IF, while also allowing us to identify and understand differences between a one-time, high-intensity screening in a generally healthy population (CRC) and repeated cancer screening in a more medically complex population (HCC).

There is equipoise about which strategy will work better. IF works by addressing provider and site barriers. With facilitator support, sites build an internal team, identify strengths and barriers, and select the approach that will work to improve implementation. In contrast, PN focuses on overcoming patient barriers to seeking care. Navigators work directly with patients, which can circumvent barriers of awareness, education, and buy-in. A systematic review of 25 studies found that IF improved cancer screening by an average of 5%–8%;[78] CRC screenings have been increased up to 11% using IF [32, 40]. While both IF and PN are evidence-based, they also have potential disadvantages in certain settings [27, 79–81]. PN has improved HCC and CRC screening, including colonoscopy after positive stool test [82–87]. Our study will evaluate for what type of site (specialty care availability and other organizational characteristics), what type of patient (who benefits most and least) and when (for a one-time screening vs. ongoing screening) PN or IF work better to promote screening and improve patient reported outcomes.

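### The primary model puts a Veteran random effect in both trials, but the CRC outcome normally gives one binary record per Veteran, so that variance is not identified in CRC

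*Protocol article*

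**What the plan says.** The Analysis section of the protocol article gives a single description of the primary model, and nothing in it separates the two trials:

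- Fixed effects: "Time, intervention status, and the interaction will be modeled as fixed effects".
- Random effects: "Random effects will be included for clustering by site and Veteran".
- Estimation: "variance components will be estimated using the Maximum Likelihood or Restricted Maximum Likelihood". The Veteran variance is therefore to be estimated, not fixed.

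Other sections treat the two trials differently on this very point:

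- Outcomes, for CRC: "we will assess whether patients with an abnormal stool-based CRC screening test completed a colonoscopy within six months". Table 2 gives the time points for reach as "Baseline & 12 months".
- Discussion, setting CRC against repeated HCC screening: "a one-time, high-intensity screening in a generally healthy population (CRC".
- Sample size and power: "within-person correlation of 0.2 (for HCC"; no such value is given for CRC.
- Inclusion and exclusion criteria, for CRC: an abnormal FIT "or other screening stool test in the last 18 months".

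**The concern.** A Veteran random intercept describes correlation between repeated results from the same person. Where a person contributes one binary result, there is nothing to correlate, and a Veteran-level variance cannot be told apart from ordinary Bernoulli variation. The CRC outcome normally has this form. The planning inputs reflect that, but the analysis sentence does not.

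Two things are at stake. A conditional arm-by-time odds ratio from this model would depend on where the software stops on the Veteran variance. The same model is also reused for the heterogeneity analyses and then fitted separately by subgroup, so CRC subgroup odds ratios could rest on different variance values and not be comparable.

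A second question follows from the 18-month look-back. The text does not say whether it is applied again at 12 months. If it is, some tests are counted in both periods.

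**Working it through.** **The plan's own figure.** The stated CRC power (over 80% with 16 sites per arm) cannot be reproduced exactly, because neither the baseline rate nor the correlation of site effects over time is given. With a site effect constant over time, mean cluster size 429, ICC 0.03, an IF gain of 0.09 and an assumed two-sided alpha of 0.05, power for 0.085 is about 1.00 at every baseline rate from 0.2 to 0.7. That is consistent with the claim, but it does not bear on the point here.

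**One record per Veteran.**

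Inputs from the protocol: 16 sites per arm, 429 patients per site, a difference of 0.085 and an IF gain of about 9%. Assumed: 50% at baseline, a logit link and equal numbers in both periods. The rates are then 50% at baseline, 59% in IF and 50% + 9% + 8.5% = 67.5% in PN. Each arm and period has N = 16 × 429 = 6,864 records. The site effect is left out at first.

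The marginal probability in a cell is π(η, σ) = ∫ expit(η + σz) φ(z) dz. The log-likelihood is the sum over four cells of N[p log π + (1 − p) log(1 − π)]. Four fixed-effect parameters describe four cells, so for any σ the η values can be chosen to make π = p in every cell. The maximum is therefore the same for every σ. The interaction is (η for PN at 12 months − η for PN at baseline) − (the same for IF). At σ = 0 it is logit(0.675) − logit(0.59) = 0.731 − 0.364 = 0.367.

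| Veteran SD | Max. log-likelihood | Interaction log-OR | OR | Rate difference |
|---|---|---|---|---|
| 0 | −18489.79 | 0.367 | 1.44 | 0.085 |
| 1 | −18489.79 | 0.440 | 1.55 | 0.085 |
| 2 | −18489.79 | 0.597 | 1.82 | 0.085 |
| 3 | −18489.79 | 0.787 | 2.20 | 0.085 |
| 4 | −18489.79 | 0.990 | 2.69 | 0.085 |

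**With site effects and unequal clusters.** One simulated trial had 32 sites, cluster-size CV 0.631, ICC 0.03 and one record per Veteran. The Veteran variance was fixed at values from 0 to 9.

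- The log-likelihood stayed between −16026.02 and −16026.21, a range of 0.19.
- The log-OR rose from 0.365 to 0.782.
- The marginal difference in change stayed at 0.083 to 0.085, and the interaction z at 6.84 to 6.95.

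**Under the Laplace approximation**, with the inputs of the table, the profile is not flat: −18489.79 at SD 0, −18669.67 at 1, −19215.27 at 2 and −19719.0 at 4. The estimate goes to zero and the OR is 1.44, as in a model with no Veteran term.

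**If the look-back is applied at both time points.** The windows run from −18 to 0 and from −6 to 12 months around baseline. They share 6 of 18 months, one third. Suppose one third of the records in each period are the same tests, with a 50% rate and the same outcome both times. The rate difference falls to (2/3) × 0.085 = 0.057 before any Veteran term is added. Adding the term gives:

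| Veteran SD | Log-likelihood | log-OR | Rate difference | z |
|---|---|---|---|---|
| 0 | −18793 | 0.23 | 0.057 | 4.8 |
| 4 | −16556 | 0.46 | 0.041 | 4.1 |
| 8 | −16124 | 0.65 | 0.031 | 3.5 |

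The likelihood keeps rising over this range, so maximum likelihood pushes the variance upward. If some pairs go from not completed to completed, the likelihood still favours a large variance and the rate difference still drops, to about 0.025 to 0.03.

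**The case against.** The strongest reply is that the test and the target scale are safe. With one record per Veteran, the rate difference and the interaction z barely move whatever variance is returned. The Analysis section names neither a link nor an odds ratio, and the effect summary it does give, for subgroups, is a difference in change. This stands. A reader might infer that the CRC model would not measure the rate difference on which the trial is powered; with one record per Veteran, the calculations show otherwise.

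A reader might also infer that the model must fail to converge. The documents do not support that, because the integration method is not stated. Under Laplace the fit may simply collapse to the model without a Veteran term.

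Next, one record per Veteran is an inference. A Veteran with two separate abnormal tests would have two rows, which is a fair reason to think about within-person correlation. The 18 months is an eligibility rule, and no section says that it is re-applied at 12 months or that a test counts twice. That also stands, so the overlap result is conditional.

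Finally, one sentence in a condensed article may be meant to apply only where results repeat, with details left to an analysis plan. The authors clearly know the distinction. But the sentence states a model term for both primary analyses without restriction, and for CRC that term does not fit the outcome described. This is stated text that needs a limit, not a missing detail.

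**Conclusion.** The point holds in a limited form. The stated Veteran random effect does not suit the CRC outcome and is out of step with the HCC-only within-person correlation in the power section.

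With one record per Veteran, its variance is not identified. A conditional arm-by-time log-OR could be anything from about 0.37 (SD 0) to 0.99 (SD 4) at the same likelihood, while the rate difference and its test are essentially unaffected. The size rests on the assumed rates of 50%, 59% and 67.5% and on a logit link.

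Only if the look-back is applied at both time points does the damage reach the rate difference. Recounting alone then lowers it from 0.085 to 0.057, and the Veteran term takes it to about 0.03 at SD 8. This assumes that one third of records are duplicated.

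Nor should the correction be read as saying that site terms absorb within-Veteran correlation. They do not, so Veterans who appear in both CRC periods need a separate check. The change is worth making before outcome data are analysed.

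**What to change.** Limit the Veteran random effect to the HCC model. For CRC:

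- Enter each abnormal stool test once, assigned to one period by its test date, with one index test per Veteran per period.
- Fit site-level random terms without a Veteran intercept.
- Use site-level cluster-robust standard errors as a check, to cover Veterans who appear in both periods.
- Report the arm difference in change as a rate difference with 95% CI, the scale of the 0.085 target.

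The cost is a few sentences of analysis wording. No new data are needed, and the number of sites does not change.

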### Methods to address limitations

We will assess the robustness of the conclusions using sensitivity analyses and report on all patients, any reasons for dropout, and differences in dropout by patient and site characteristics. Since our primary outcomes will be assessed using VA Corporate Data Warehouse data, we anticipate negligible missingness in the primary outcome of cancer screening completion. Non-screening will be assumed for those without confirmed screening. During the data collection, we will reduce missingness (to the extent possible) in covariates, using additional data sources with more complete data. If the missing proportion is high (e.g., > 5%), we will conduct a sensitivity analysis to assess the impact of the missing data on the primary analysis results and model the missing data mechanisms using established methods. Demographic characteristics and key clinical outcomes will be compared between the subgroup with complete vs. incomplete data, and all sensitivity analysis results will be reported. To address challenges with survey response rates, we will follow guidance about provider and patient surveys from the literature and our Veteran Advisory Board, centering research reciprocity, ensuring clarity, and minimizing survey burden. Despite our focus on US Veterans, these trials were designed to offer generalizable findings for community settings and non-Veterans. The mechanisms and comparative effectiveness of different implementation strategies are of interest beyond VA, and VA-generated implementation science methods and findings have often successfully translated to non-VA settings.

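### As written, the primary CRC analysis sets no minimum follow-up after the abnormal stool test, so Veterans with an open six-month window and no colonoscopy yet count as failures

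*Protocol article*

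**What the plan says.** Five statements in the Protocol article bear on this.

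- **Inclusion and exclusion criteria:** the CRC trial takes "Veterans over 45 years old who have had an abnormal fecal immunochemical test (FIT) or other screening stool test in the last 18 months". No minimum time since the test is given.
- **Outcomes:** for CRC, "we will assess whether patients with an abnormal stool-based CRC screening test completed a colonoscopy within six months". The primary comparison is made "at 12 months from baseline".
- **Analysis, primary model:** "We will use generalized linear mixed models (GLMMs) to assess the primary outcome of reach at 12 months". Time, arm and their interaction are fixed effects. No follow-up restriction is stated.
- **Analysis, same paragraph:** "We will conduct a secondary analysis of the CRC outcome evaluating time to colonoscopy after abnormal stool test", and in the same sentence the authors will "conduct a sensitivity analysis that includes only Veterans with at least six months of follow-up after stool testing".
- **Methods to address limitations:** "Non-screening will be assumed for those without confirmed screening".

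**The concern.** A six-month outcome is unknown until six months have passed or the colonoscopy has been done. For a Veteran tested two months before the data cut and not yet scoped, it is undetermined. The stated rules nevertheless keep that Veteran and score non-screening. The set in which every outcome is known appears only as a sensitivity analysis.

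Three things are at stake in the primary CRC result. Reach is understated in both arms. The difference between patient navigation and facilitation shrinks with it. And the measure mixes speed with completion: two arms with the same six-month completion would show different reach if one schedules colonoscopies sooner. The sensitivity and time-to-event analyses could reveal these effects but do not correct the primary estimate.

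**Working it through.** **Inputs from the Protocol article:** look-back 18 months; outcome window 6 months; target difference 0.085; 16 CRC sites per arm; mean 429 eligible patients per site; coefficient of variation of cluster size 0.631; ICC 0.03.

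**Assumed, because the article does not give them:** even accrual of stool tests; the timing of colonoscopies within six months; a cohort that rolls forward with the same look-back; two-sided alpha 0.05; 50% baseline rate; between-period site correlation 0.8.

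**Step 1. Open windows.** The share of tests under six months old at a data cut is 6/18 = 0.333. Only those not yet scoped are misscored; Veterans already scoped count as screened.

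**Step 2. Share of true reach retained.** Let g be the average fraction of eventual six-month colonoscopies already done among open windows. Retained share r = 1 − (6/18)(1 − g).

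| Colonoscopies spread evenly over | g | r | 60% reads as | 0.085 reads as |
|---|---|---|---|---|
| months 0–6 | 0.500 | 0.833 | 50.0% | 0.071 |
| months 0–3 | 0.750 | 0.917 | 55.0% | 0.078 |
| months 1–4 | 0.583 | 0.861 | 51.7% | 0.073 |
| months 3–6 | 0.250 | 0.750 | 45.0% | 0.064 |

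**Step 3. Speed only.** Both arms truly reach 60% at six months, one over months 0–4 (g = 0.667, r = 0.889) and the other over months 0–6 (r = 0.833). Observed reach is 0.6 × 0.889 = 0.533 against 0.6 × 0.833 = 0.500. The apparent difference is 3.3 percentage points where six-month completion is equal.

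**Step 4. Power, illustrative.** The stated figure is above 80% with 16 sites per arm. It cannot be reproduced exactly, because baseline rate, alpha and between-period correlation are not given. A normal approximation for a difference-in-differences, with p(1 − p) = 0.25 throughout, has variance

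(2/16) × [2 × 0.25 × 0.03 × (1 − 0.8) + 2 × 0.25 × 0.97 × (1 + 0.631²)/m].

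- Undiluted, m = 429: SE = 0.0239; 0.085/0.0239 = 3.55; power about 0.94, compatible with the stated figure.
- Open windows kept, m = 429, difference 0.0708: ratio 2.96; power about 0.84.
- Closed windows only, m = 429 × 2/3 = 286, difference 0.085: SE = 0.0259; ratio 3.28; power about 0.91.
- Tests from intervention months 0–6 only, m = 429 × 6/18 = 143 if 429 is an 18-month count: SE = 0.0311; ratio 2.73; power about 0.78.

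**Step 5. Cohort fixed at baseline.** The latest test is at month 0, so every window has closed by month 6 and none is open at month 12. At baseline the open share is still 6/18 under even accrual. The baseline rate is then understated and the 12-month rate is not, so part of the change over time is an artefact of scoring.

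**The case against.** The article never names the primary CRC analysis set, and a condensed article may leave denominators to a fuller plan. The follow-up restriction shares a sentence with the time-to-event analysis and may belong to it, or it may be meant to exclude Veterans who died or left VA care. The non-screening rule sits in a paragraph on missing records, not on unfinished windows. The scoring is the same in both arms, so the main effect is conservative, and the illustrative power of 0.84 still exceeds 80%. Two planned analyses would expose a difference in speed.

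Much of this stands and limits the point. It does not remove it. Time-to-event methods already handle short follow-up by censoring, so the restriction fits the binary outcome better. On either reading, no restriction is stated for the primary model. The non-screening rule has no exception for unfinished windows.

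A reader might infer three stronger claims that the documents do not support:

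- *That one third of the cohort is affected at every assessment.* This needs a rolling cohort and even accrual, neither of which is stated. The Veteran random effect suggests repeated measures on one cohort, while the within-person correlation is quoted for HCC only. In a fixed cohort the open share at month 12 is zero.
- *That all Veterans with open windows are miscounted.* Those already scoped are counted correctly.
- *That the comparison is biased between arms.* This needs the arms to differ in speed or in the timing of stool tests. It is possible, but the article gives no figure for either.

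**Conclusion.** The point holds in limited form. Taken together, the eligibility, outcome, analysis and non-screening statements set no minimum follow-up for the primary CRC analysis and score undetermined outcomes as failures. Understatement of reach wherever windows are open follows from the rules as written; its size rests on assumptions.

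- **Rolling cohort, 18-month look-back, even accrual:** up to one third of windows are open at each assessment. Measured reach is 75% to 92% of the truth, and 0.085 reads as 0.064 to 0.078, centrally 0.071. A difference in speed alone could also appear as a difference in reach.
- **Cohort fixed at baseline:** the 12-month measurement is unaffected, but the baseline in the time-by-arm model is understated and the two time points are not comparable.

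The loss of power is moderate in the illustration (0.84 against 0.91). The stronger reason to act is that the primary estimate does not measure the outcome as defined.

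**What to change.** State the primary CRC denominator and the dates of the index stool tests at each time point. Then take one of two routes.

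1. At both time points, restrict the primary denominator to Veterans whose six-month window after the index test has closed at the data cut, selecting index tests by the same look-back rule each time. Move the unrestricted set to the sensitivity analysis and keep time to colonoscopy as secondary. Index tests must be selected afresh at each cut: in a fixed cohort, a window already closed at baseline has an outcome that can no longer change.
2. Keep the included tests and ascertain colonoscopy from the medical record until six months after the last one, using the follow-up at 6 months post already planned under Maintenance in Table 2. Baseline tests should then end six months before the start, so that their windows do not run into the intervention.

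Do not limit the primary analysis to tests from intervention months 0–6. That cuts the sample by about two thirds if 429 is an 18-month count (power about 0.78), and it samples only the six months in which facilitation sites are working through their regular meetings.

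Cost: route 1 loses about one third of CRC Veterans per assessment. With an 18-month look-back, its month-12 set covers tests from month −6 to month 6, so under even accrual half were done before the start and had only part of their window under the intervention. The power figures do not allow for this. Route 2 avoids the loss of Veterans but delays the primary read-out by six months, past the 12-month time point now stated. Either change should be made before outcome data are seen.
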